## Methods/Design

### The SASA! intervention

SASA! - *An Activist Kit for Preventing Violence against Women and HIV *[43], was designed by Raising Voices and is being piloted and implemented by the Centre for Domestic Violence Prevention (CEDOVIP) in Kampala. The intervention uses a community mobilisation approach to try to change the community attitudes, norms and behaviours that underlie power imbalances between men and women and support both HIV risk behaviours and the perpetration of violence against women. The intervention takes a holistic approach, that explicitly recognises that IPV is the result of a complex interplay of factors operating at the individual, relationship, community and societal levels [44] - therefore interventions to prevent it must engage with and achieve change at each of these levels (see Figure 1).

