### Evaluation design

The study employs a matched cluster randomised design, with randomisation carried out within matched community pairs. As described previously, the comparison groups comprise four intervention communities (receiving the full intervention) and four control communities (receiving only Division level elements of the intervention) (Figure 3). Quantitative data collection will occur before (baseline) and four years after (follow-up) implementation of the intervention. It is important to note that a four-year follow-up period does not equate to four years of programming - barriers to programme activity including political disturbances and the suspension of activities during political election campaigns, mean that the duration of SASA! programming will have been approximately 2.8 years by the time of the follow-up survey. At each time-point, data will be collected from a cross-sectional sample of community members targeted by the intervention, and from community activists.

The primary analysis will compare intervention and control communities at follow-up. This protocol focuses on the CRT element of the evaluation that will assess the impact of the intervention on the outcomes identified in the first trial objective. However, in addition to this, monitoring and evaluation data will be collected throughout the duration of the study, including through repeated rapid assessment surveys of community members. These data will be used to document, among other things, how the intervention is implemented, its evolution in different communities, CA retention/turnover, the people it reaches, diffusion of activities into control communities, barriers to intervention delivery, and other relevant activities and policy changes that occur over the time period of the study.

A complementary ongoing programme of qualitative data collection will also allow more in-depth understanding of the implementation and processes of the intervention, including community perceptions of it, the forms of behaviour change being promoted, and the ways in which change is occurring at different levels and among different groups.

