### Site selection and randomisation

Kampala comprises five administrative Divisions. While some SASA! components occur at Division-level, the majority of intervention activities are implemented in more circumscribed communities or sites. Two neighbouring Divisions were purposively chosen for implementation of the Division-level components of SASA!. Within these, eligible sites were identified on the basis of operational and programmatic considerations. Factors considered when delineating eligible sites included population density, geographical area, socioeconomic characteristics, and accessibility to the CEDOVIP office. Eight eligible sites, each comprising one or two parishes, were identified for the study. All were separated from each other by a geographical buffer (at least one parish wide) to reduce the potential for contamination between intervention and control communities.

Sites were matched into four pairs on the basis of qualitative assessments by CEDOVIP staff as to whether the site was densely populated urban or semi-rural, and assessments of the stability/mobility of the local population.

Within each pair one site was randomly selected to receive the complete intervention from the outset of the study, and the other was designated as a control that would receive the full intervention at the end of the study. The randomisation process was conducted in September 2007. The names of the two communities within a matched pair were written on identical pieces of paper which were then folded and put in a bag. One paper was blindly drawn from the bag. The selected name was assigned as an intervention community. Control communities have been receiving Division-level components of the intervention from the outset of the study.

Interviewers conducting the baseline survey were blinded to the allocation of the intervention. However, at follow-up it will not be possible to keep interviewer teams blinded.

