### Outcomes

Outcomes will be measured four years after implementation through use of an interviewer administered survey. As described previously, due to external factors forcing intermittent interruptions in programme activity, this four year follow-up period equates to approximately 2.8 years of SASA! programming.

The primary outcomes for this study are presented below, along with the hypothesised direction of intervention effect for each:

Acceptability of intimate partner violence (among all women; all men) (decrease);

Acceptability that a woman can refuse to have sex (among all women; all men) (increase);

Past year experience of physical violence from a partner (among women who have had an intimate partner in the past year) (decrease);

Past year experience of sexual violence from a partner (among women who have had an intimate partner in the past year) (decrease);

Appropriate community response to women experiencing physical and/or sexual IPV in past year (among women who experienced physical and/or sexual IPV in past year) (increase);

Past year concurrent sexual partners (among non-polygamous partnered men) (decrease).

Further discussion on the measurement of outcomes is detailed below.

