**Figure 6 F6:**
[figure not shown]
Items used to create composite outcomes for physical and sexual intimate partner violence.

Female reports of experience are chosen over male reports of perpetration because it is anticipated that men are more likely to give socially desirable responses about their own behaviour and thus under-report perpetration. Indeed baseline data from this study revealed that male reports of perpetration were considerably lower than female reports of experience, particularly for the more severe acts [47].

Questions on violence are asked in accordance with international guidelines for the collection of data on violence against women [56]. These guidelines seek to minimise reporting bias and risk of harm posed to the respondents and interviewers involved in the survey. Interviewers, all from the local community, will undergo at least 3 weeks of preparatory training on ethical and methodological issues surrounding the conduct of a survey relating to IPV and HIV. This includes sessions on how to ensure the privacy, confidentiality and safety of the respondent, how to build rapport, and how to talk about difficult topics in a non-judgmental, sensitive and supportive manner. Interviews are conducted in Luganda or English.

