#### Appropriate community response to women disclosing violence

This outcome will be measured among women reporting past year experience of physical and/or sexual IPV. Respondents will be asked: ‘When the experiences you have told me about were happening or afterwards, did anyone in your community try to help you?’ (yes/no). Those answering in the affirmative will then be read a series of questions on how that person/those people tried to help them. If the respondent reports that someone tried to help them, and they did so with at least one appropriate response, this will be coded as an appropriate community response. If the respondent reports that no one tried to help them or no one took any appropriate action or offered appropriate advice, this will be coded as a negative response. Appropriate responses reflect actions encouraged by the intervention and include someone taking the following actions: gathering other people from the community to help; knocking on the door to stop the fighting; separating the woman and her partner during fighting; informing the CA, ssenga, LC, police or other authority; talking to the woman afterwards and asking her if she wants them to help; or telling the woman to talk to someone else such as a family member, friend, community activist, LC, ssenga or other authority figure.

When interpreting results for this outcome, it is necessary to consider the complications in inference that arise when measuring intervention impact on a positive outcome that is contingent on a negative outcome (IPV) occurring. If the intervention is successful in reducing violence, then the mix of cases of violence which remain in intervention communities (and thus for which we can measure community response) may not be comparable to the mix of cases of violence occurring in control sites. They may, for example, comprise those cases that are the most hidden, and therefore least likely to elicit a community response (this in itself being a potential reason why the violence has persisted). We therefore surmise that our estimates of intervention impact for this outcome will be conservative, and we can assume a greater effect than that which we are able to observe.

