An additional complicating factor related to duration of intervention exposure is that the study is conducted in highly mobile populations. This, coupled with the cross-sectional design of the follow-up survey, means we may survey people who have not been exposed to the intervention for an extended period. Although we attempt to overcome this problem by restricting eligibility to those who have lived in their village for at least one year, if the intervention takes longer than a year to have an impact, high levels of population mobility might affect the study’s capacity to detect an impact. This limitation is not specific to the evaluation design but instead pertains to whether the intervention itself can promote community-wide change in an unstable population. The SASA! study will thus answer the question whether a community-level impact can be observed despite high levels of mobility, rather than measure the potential efficacy of the intervention given ideal experimental conditions.

The above limitations would lead us to underestimate any true potential (or adverse consequences) of the SASA! intervention, and should therefore be borne in mind when interpreting null associations, rather than invoked to undermine observed intervention effects.

The repeated cross-sectional design is arguably a further limitation. While baseline data will allow us to assess the comparability of areas at baseline (and control for differences in the analysis), the cross-sectional nature of the follow-up survey makes it harder to definitively separate intervention effects from the effects of changes in population make-up during the course of the study, especially if population mobility is high. As discussed, the most likely way that random population changes would influence effect estimates is to bias them towards unity. The repeated cross-sectional design was chosen in preference to a cohort study as the latter was deemed both impractical in this high mobility setting, and subject to selection bias from excessive levels of attrition. The cross-sectional design also suits our objective to measure community- rather than individual-level intervention impact.

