Finally, as with many trials of community-based interventions, the number of communities randomised is low. Our effect estimates may therefore have relatively low precision, particularly if there is a high level of clustering of outcomes or effect sizes are small. The rigorous design will, however, produce unbiased estimates of impact, and we will thus focus on the consistency, congruency and plausibility of results rather than the statistical significance of individual effect estimates.

Although subject to several limitations, the SASA! study is one of a small number of cluster randomised trials to assess the impact of this type of community-based intervention on IPV and sexual behaviour. The intervention consists of a combination of complementary components, implemented by a wide range of community actors. In contrast to many other health promotion approaches, the focus of the intervention is to support a process of change at a community level, with the aim of sensitising, engaging with and mobilising communities to address gender norms, violence and HIV risk behaviours in their communities. For this reason, the specifics of some of the intervention activities are not proscribed on a per protocol basis, but rather develop and evolve in direct response to community priorities, needs and issues. In designing the SASA! study, we faced not only the usual logistical constraints, but also the difficulties of implementing such a holistic and broad intervention within the context of a randomised trial. We chose to restrict the trial to a small number of sites, placing emphasis on intervention quality and adherence to the trial protocol. The CRT will be complemented by an ongoing process evaluation and programme of qualitative research. This will allow us to address questions not only of intervention impact and mechanisms of action, but also its feasibility, acceptability, potential transferability to other contexts and cost.

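### The Discussion claims unbiased estimates and rests its reading of the results on that, but unblinded interviewers collect all six self-reported primary outcomes, so reporting may differ by arm

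*Protocol article*

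**What the plan says.** The last limitation in the Discussion concerns the small number of communities. It concedes low precision and then states "The rigorous design will, however, produce unbiased estimates of impact". The same sentence draws the consequence that attention will go to consistency, congruency and plausibility rather than to the significance of single estimates. The section on coherence and plausibility versus statistical significance says the same: changes in the expected direction across all outcomes, largely coherent with one another, are to support a plausible case for impact.

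On measurement, the article says:

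- Evaluation design: "The primary analysis will compare intervention and control communities at follow-up".
- Site selection and randomisation: interviewers were blinded at baseline, but "at follow-up it will not be possible to keep interviewer teams blinded".
- Outcomes: "Outcomes will be measured four years after implementation through use of an interviewer administered survey".
- The SASA! intervention: "The intervention uses a community mobilisation approach to try to change the community attitudes, norms and behaviours".
- Community response outcome: "Appropriate responses reflect actions encouraged by the intervention".
- Measures of IPV, explaining why women's reports are used: "it is anticipated that men are more likely to give socially desirable responses about their own behaviour".

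After listing contamination, Division-level components in control sites, short follow-up and mobility, the Discussion says that these limitations "should therefore be borne in mind when interpreting null associations, rather than invoked to undermine observed intervention effects". Its paragraph on measurement bias relies on standardised questions and interviewer training.

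**The concern.** A claim of unbiased estimates covers measurement as well as allocation. Here the outcome data come from interviews by people who know the arm. In intervention sites the respondents have been exposed to messages about the same attitudes and behaviours. Standard questions, privacy and training reduce reporting error in general, but they do not ensure that the remaining error is equal in the two arms. The article discloses the loss of blinding in Methods and does not carry it into the limitations.

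This matters because the claim is used as a premise. With four sites per arm, the plan relies on direction and coherence across outcomes. Outcomes measured in the same unblinded interview can share a reporting bias, and a shared bias can produce agreement in direction without any true effect. Where reporting moves the other way, a real benefit could be missed.

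**Working it through.** **1. Does the claim follow from the design?** No figure is in dispute, so this is settled by reading.

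| Element | What the article provides | Protects against reporting that differs by arm? |
|---|---|---|
| Random allocation within pairs | Removes placement bias | No |
| Baseline survey | Interviewers blinded | No, the primary comparison is at follow-up |
| Adjustment for baseline prevalence, age and sex | Corrects imbalance | No, the difference would arise at follow-up |
| Standard questions, training, privacy | Reduce error overall | Not as such |
| Limitations in the Discussion | Dilution, population change, few clusters | Not mentioned |

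The claim is therefore sound for allocation only.

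**2. Which direction?**

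- Acceptability of violence, acceptability of refusing sex, male concurrency: the approved answer is what the intervention promotes, so movement in the hypothesised direction is plausible.
- Physical and sexual IPV: the Support phase encourages people to seek help, and the intervention seeks recognition of sexual coercion as violence. Both could raise disclosure in intervention sites and mask benefit. Women could also under-report.
- Community response: the coding follows the intervention's own messages, but the denominator depends on disclosure of IPV. The direction is unclear.

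**3. How large could it be? (illustration)** The article gives no differential reporting rate. Let r be the assumed fraction of intervention-arm respondents who deny an undesirable outcome that they would have reported in a control site. With no true effect the prevalence ratio is 1 − r. This form applies to outcomes expected to decrease, not to the two expected to increase.

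The variance was first checked against the plan's own tables. For a risk difference with four sites per arm and t on 6 df (2.447):

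SE² = [p0(1−p0)/n + p1(1−p1)/n + k²(p0² + p1²)]/4

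- Table 1, 30% v 22.5%, n = 75, k = 0.1: SE² = (0.002800 + 0.002325 + 0.001406)/4 = 0.001633, SE = 0.0404, half-width 9.9 points. The interval is −2.4 to 17.4, as printed.
- Table 2: the just-significant differences come to about 8.6, 6.3 and 14.5 points, against 9, 7 and 15 stated. They agree if rounded up.

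On the log scale, which the primary analysis uses:

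SE² = [(1−p0)/(n p0) + (1−p1)/(n p1) + 2k²]/4

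Example, physical IPV, p0 = 0.23, n = 72, k = 0.1, r = 0.20, p1 = 0.184: SE² = (0.0465 + 0.0616 + 0.0200)/4 = 0.0320, SE = 0.179. Then ln(0.8)/SE = −1.247. The chance of an estimate below 1 is Φ(1.247) = 89%. The chance of a significant benefit, from the noncentral t on 6 df, is 18%.

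| Outcome (no true effect) | Inputs | Significant benefit at r = 10%, 20%, 30% | Estimate in hoped-for direction at r = 20% |
|---|---|---|---|
| Physical IPV | 23%, n = 72, k = 0.1 (Table 2 gives k below 0.1) | 7.5%, 18%, 36% | 89% |
| Sexual IPV | 12%, n = 72, k = 0.16 (Table 2) | 5.3%, 11%, 19% | 80% |
| Concurrency | 45%, n = 83, k = 0.17 (Table 2) | 8.6%, 23%, 48% | 93% |
| Women accepting violence | 73%, n = 150, k = 0.1 (assumed) | 20%, 62%, 94% | 99.7% |

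Without bias the two chances are 2.5% and 50%. The 73% is the national survey figure in the study setting section. The trial uses its own 12-scenario measure, so this row is the loosest. The n of 150 is the follow-up target: 2,400/8 sites/2 sexes.

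**4. The opposite direction.** Suppose physical IPV truly falls by the detectable 39% (ratio 0.61), and women in intervention sites disclose 20% more (assumed). The expected ratio is 0.61 × 1.2 = 0.73. With the same inputs, the chance of a significant result drops from about 57% to about 30%.

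**The case against.** The strongest reply is that unblinded self-report is largely unavoidable here and is disclosed in Methods. The article also asks about specific acts in non-leading terms, uses private same-sex interviews and trains interviewers for three weeks. In context the sentence contrasts bias with imprecision. All of this stands as mitigation. None of it makes the remaining error equal by arm, and the sentence is still used to justify how the results will be read.

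Several stronger readings are tempting, and the documents do not support them:

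- *Every outcome is pushed in the hypothesised direction.* A reader might infer this, but greater IPV disclosure would push the other way.
- *The article forbids questioning positive results.* The sentence saying that limitations "should therefore be borne in mind when interpreting null associations, rather than invoked to undermine observed intervention effects" covers only the dilution factors listed above it, and for those it is sound.
- *Only biases toward no effect are acknowledged.* On population change the text says only that movement toward unity is most likely, and it names non-response as a threat to validity without giving a direction.
- *Using women's IPV reports but men's concurrency reports is a contradiction.* The design offers a second informant for IPV and none for concurrency, and the remark on social desirability concerns level, not a difference between arms.
- *The bias has been measured.* It has not: r is assumed, and at 10% the shift in concurrency (0.45 × 0.10 = 4.5 points) is well below the roughly 14.5 needed for significance.

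**Conclusion.** The claim of unbiased estimates is broader than the design supports. It holds for allocation of the intervention. It does not hold for outcomes self-reported to unblinded interviewers, and the article rests its coherence-based interpretation on it. Bias away from the null is plausible for the attitude outcomes and male concurrency. For IPV it could go either way.

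The size is unknown. Under assumed differential reporting of 10% to 30%, the false-benefit rate rises from 2.5% to between 5% and 48% for the IPV and concurrency outcomes, and further for attitudes on looser inputs. Direction is affected more readily than significance, and direction is what the plan emphasises. These figures rest on the assumed r, on an assumed k for attitudes, and on baseline prevalence and cluster sizes for the IPV and concurrency rows. They show that the effect could matter, not that it is present. The correction should be made, and it costs almost nothing.

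**What to change.** Three text changes:

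1. In the Discussion, limit the word unbiased to the allocation of the intervention.
2. Add unblinded, interviewer-administered self-report to the limitations as a possible bias in either direction. State that the sentence about not undermining observed effects does not extend to it.
3. In the coherence and plausibility section, and where the Discussion repeats it, state that agreement in direction across outcomes sharing this measurement is not independent evidence of impact. State also that a benefit seen only in the attitude and male-concurrency self-reports will be reported as possibly due to reporting.

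The downside is a slightly more cautious conclusion. No new data are needed. Balancing interviewers across the two sites of a pair is optional: it would even out differences between individual interviewers but would neither blind them nor change how respondents answer. The article may simply omit such field detail.
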